## **11.3 Serious Adverse Events**

Serious Adverse Events (SAEs) that result in or lead to one or more of the following and the event is **not related** to the trial intervention:

- The death of a trial participant.

- A life-threatening illness or injury involving a trial participant.
- A participant's permanent impairment of body structure or body function.
- In-patient or prolonged hospitalisation (not for a pre-existing condition or an elective surgery) of a trial participant.
- Medical or surgical intervention to prevent life-threatening illness or injury or permanent impairment to a body structure or function of a trial participant.
- Fetal distress, fetal death or congenital abnormality or birth defect.

SAE reports are classified following the safety assessment flowchart and are assessed by Sponsors Independent Medical specified in section 2 of the protocol. The Sponsors Independent Medical cannot delegate this responsibility to other research personnel. SAE reports are reported to the Coordinating Principal Investigator immediately or within 24 hrs of the event occurring. SAR reports must be recorded in the [UNSW Safety Monitoring Register Template](#).

#### 11.4 Serious Adverse Reactions

A Serious Adverse Reactions (SAR) is an SAE that is **related** to the trial intervention. SAR reports are classified following the safety assessment flowchart and are assessed by Sponsors Independent Medical expert specified in section 2 of the protocol. The sponsors independent medical expert must determine whether the SAR was expected or unexpected. The Sponsors Independent Medical cannot delegate this responsibility to other research personnel.

##### a) Expected Serious Adverse Reaction

A serious adverse reaction by its nature, incidence, severity, or outcome is anticipated and identified in the current version of the intervention safety information is classified as a SAR report. SAR reports are reported to the Coordinating Principal Investigator, immediately or within 24 hrs of the event occurring. Serious Adverse Reaction reports must be recorded in the [UNSW Safety Monitoring Register Template](#).

##### b) Suspected Unexpected Serious Adverse Reaction (SUSAR)

A serious adverse reaction by its nature, incidence, severity, or outcome is unanticipated and not identified in the intervention's instructions for use or safety information is classified as a SUSAR.

Fatal or life-threatening Australian SUSAR reports are reported to the Coordinating Principal Investigator, the sponsor's delegate and the approving HREC within 7 calendar days after being made aware of the case follow up information reported within a further 8 calendar days.

All other Australian SUSAR reports are to be reported to the Coordinating Principal Investigator, the sponsor's delegate and the approving HREC within 15 calendar days after being made aware of the case follow up information reported within a further 8 calendar days. SUSAR reports must be recorded in the [UNSW Safety Monitoring Register Template](#).

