## **11.2 Adverse Events or Adverse Reactions**

Adverse events (AE) are considered any untoward medical occurrence in a patient or clinical trial participant administered the intervention, which does not necessarily have a causal relationship with this treatment.

Adverse Reactions (AR) are considered untoward and unintended responses to the trial intervention related to any intervention procedures.

AEs and ARs are assessed using the safety monitoring flow chart. Those classified as "not serious" are assessed by the qualified physician/medical expert specified in section 2 of the protocol. The Qualified Physician cannot delegate this responsibility to other research personnel.

Adverse event reports must be reported to the Principal Investigator within 24 hours of being notified by the participant. All adverse event reports must be recorded in the [UNSW Safety Monitoring Register Template](#).

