## 10.2 Serious Breach of Good Clinical Practice

A serious breach is defined as a breach of Good Clinical Practice, the clinical trial protocol, the clinical trial standard operating procedures, or the human ethics approval that is likely to affect to a significant degree the safety or rights of participants or the reliability and robustness of the data generated in the clinical trial. Examples of serious breaches include but are not limited to:

- Persistent or systematic non-compliance with the instructions for completing consent forms, safety monitoring forms, case report forms or data collection tools that result in continued missed or incomplete data collection.
- Failure to record or report adverse events, serious adverse events, suspected unexpected serious adverse reactions, significant safety issues where urgent safety measures were implemented.
- Failure to conduct clinical trial procedures following the clinical trial delegation log.
- Widespread and uncontrolled use of protocol waivers affecting eligibility criteria, which leads to harm to trial subjects.
- Failure to report investigational medical product or device defects to the clinical trial sponsor or any relevant regulatory body.
- Failure to conduct research following the issued approvals, permits or licences by required laws, regulations, disciplinary standards, and UNSW policies relating to the responsible or safe conduct of research.
- Concealing or facilitating breaches (or potential breaches) of the Research Code by others.
- Researching without the requisite approvals, permits or licences required by laws, regulations, disciplinary standards, and UNSW policies related to the responsible or safe conduct of research.
- Failure to conduct research as approved by an ethics review body where that conduct leads to (or has the potential to) results in participant harms.
- Researching without ethics approval as required by the National Statement on Ethical Conduct in Human Research where that conduct leads to (or has the potential to) result in participant harms.
- Any breaches as outlined in the UNSW Research Misconduct Procedure or the Australian Code for responsible conduct of research that leads to (or can potentially) result in participant harms.

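### Sections 11.2 to 11.4 disagree on recipient, time limit and clock start for serious events, so a related, unexpected serious reaction has the slowest stated route to the Coordinating Principal Investigator

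*Protocol*

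**What the plan says.** The protocol sets a separate reporting rule for each class of event.

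- **Adverse events and reactions (11.2).** Reports "must be reported to the Principal Investigator within 24 hours of being notified by the participant".
- **Serious adverse events (11.3).** The definition lists the usual serious outcomes but adds a condition: "and the event is not related to the trial intervention". The rule is: "SAE reports are reported to the Coordinating Principal Investigator immediately or within 24 hrs of the event occurring".
- **Expected serious adverse reactions (11.4 a).** "SAR reports are reported to the Coordinating Principal Investigator, immediately or within 24 hrs of the event occurring".
- **Unexpected serious adverse reactions, SUSARs (11.4 b).** "Fatal or life-threatening Australian SUSAR reports are reported to the Coordinating Principal Investigator, the sponsor's delegate and the approving HREC within 7 calendar days", and "All other Australian SUSAR reports are to be reported to the Coordinating Principal Investigator, the sponsor's delegate and the approving HREC within 15 calendar days". Both limits are counted from awareness; for the first the wording is "within 7 calendar days after being made aware of the case".

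The opening of 11.4 defines a serious adverse reaction as a serious adverse event that is related to the intervention. Section 11.1 a) and the section on adverse event and serious adverse event reporting both state that no study-related adverse events are anticipated. The latter also says that event data come in through text, phone or email contact from participants, and that the team monitors difficulties during the training. Section 10.1 (Protocol Deviation) counts a missed reporting timeframe as a deviation.

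**The concern.** A reporting scheme normally has two layers. A fast internal step brings every serious event to the responsible investigator, and a longer external step takes classified reports to the sponsor and the ethics committee. Section 11.4 b) merges the two for SUSARs, so the class that is both related and unexpected has the longest permitted time to reach the Coordinating Principal Investigator. That is the class in which a decision about the trial is most likely to be needed.

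The second problem is the clock start. A limit that runs from the moment of the event cannot be met for an event the team hears about later. Staff who report promptly on learning of it would still be recorded as deviating from the protocol.

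**Working it through.** There is no statistical figure to reproduce. The check sets the rules side by side.

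| Class | Section | Recipient | Limit | Clock starts at |
|---|---|---|---|---|
| Adverse event or reaction | 11.2 | Principal Investigator | 24 h | participant's notification |
| Serious adverse event, unrelated | 11.3 | Coordinating Principal Investigator | immediately or 24 h | occurrence |
| Serious adverse reaction, expected | 11.4 a) | Coordinating Principal Investigator | immediately or 24 h | occurrence |
| SUSAR, fatal or life-threatening | 11.4 b) | Coordinating Principal Investigator, sponsor's delegate, ethics committee | 7 days | awareness |
| SUSAR, other | 11.4 b) | same three | 15 days | awareness |

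**Limits to the same person.** 7 days × 24 = 168 h, and 168 / 24 = 7. 15 days × 24 = 360 h, and 360 / 24 = 15. The stated limit for a SUSAR is thus 7 or 15 times that for an unrelated event or an expected reaction. No earlier internal step to this person appears in 11.4 b).

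**Which class would a related serious event enter?** Under 11.4 a), an expected reaction must be anticipated and identified in the current safety information. Section 11.1 a) names no known adverse effects, and 11.1 b) lists only risks rated mild or of minimal likelihood. If that is the safety information, the expected class is nearly empty and almost any related serious event would be a SUSAR.

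**Does the 24-hour rule in 11.3 also cover a SUSAR?** Under 11.4, a serious adverse reaction is a serious adverse event, so the answer would be yes. Under 11.3, a serious adverse event is unrelated to the intervention, so the answer would be no. The two definitions cannot both hold, and the text does not settle the question.

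**Can the occurrence-based limit be met?** Let L be the hours from the event to the team learning of it, and t the hours from learning to reporting. Sections 11.3 and 11.4 a) require L + t ≤ 24. If L exceeds 24, no t ≥ 0 satisfies this, so even an immediate report is late and becomes a deviation under section 10.1 (Protocol Deviation). Counted from awareness, the condition would be t ≤ 24, which the team can control.

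**The case against.** The strongest defence is the order of steps. An event becomes a SUSAR only after it has been reported, classified and judged unexpected. The general definition in 11.2 covers any untoward occurrence whatever its cause, so a 24-hour report to the Principal Investigator could already have been made. The Statement of Compliance moves between the coordinating and the plain title as if they were one role. There are also quicker routes. Section 11.6 requires notice to the ethics committee and the sponsor's delegate within 72 hours where an urgent safety measure is needed. The skills trainer consults the principal investigator about distressed participants, and the team watches for difficulties during training. The flow chart in 11.7 is not visible to us and may show routing.

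Much of this stands as a description of likely practice: the investigator would often hear sooner. It does not repair the text. Section 11.2 names a different role, and its assessment route is for events classed as not serious. Section 11.6 applies only where an urgent measure is required and does not name the Coordinating Principal Investigator. A flow chart could not remove contradictory wording, and its absence from our copy is not held against the plan.

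Several stronger readings are tempting and are not supported:

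- **That SUSARs arrive after 7 or 15 days, or that every clock starts wrongly.** The 7 and 15 days are upper limits, and the SUSAR clocks already run from awareness. Only 11.3 and 11.4 a) count from occurrence.
- **That the Independent Medical Expert is left out of the reporting line and alone decides relatedness.** Sections 11.3 and 11.4 name the expert as assessor. Section 11.4 expressly assigns the decision on expectedness, and the adverse event evaluation form also covers relationship to the intervention.
- **That a set number of further training sessions would run before the investigator knew.** This assumes that someone aware of the event holds the report until the last permitted day and that no quicker route operates.
- **That late reports become serious breaches.** Section 10.2 lists "Failure to record or report adverse events, serious adverse events, suspected unexpected serious adverse reactions", which is a failure to report and not lateness. The supported consequence is a deviation.

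**Conclusion.** The contradiction is real and lies in the wording. The protocol allows up to 7 or 15 days for a SUSAR to reach the Coordinating Principal Investigator, against 24 hours for an unrelated serious event or an expected reaction. Its definitions leave open whether the 24-hour rule also applies. The two occurrence-based clocks cannot be met for any event learned more than 24 hours after it happens.

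This rests on two assumptions: that 11.4 b), as the specific rule, governs SUSARs, and that the safety information lists no expected serious reaction beyond what the protocol names. The actual delay in practice cannot be estimated from the protocol and is probably shorter than the limits. Endpoints and analysis are not affected. The point is worth correcting because the rules decide who is told when, and because correction costs almost nothing.

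**What to change.** Reconcile sections 11.2 to 11.4 on recipient, limit and clock start:

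1. In 11.3, delete the restriction to unrelated events, so that the definition agrees with 11.4, where a serious adverse reaction is the related subset.
2. In 11.3 and 11.4, state one internal step for every serious event, whatever its relatedness or expectedness: to the Coordinating Principal Investigator within the protocol's own 24-hour limit, counted from the trial team becoming aware.
3. In 11.4 b), take the Coordinating Principal Investigator off the 7- and 15-day lines. Keep those lines for the sponsor's delegate and the ethics committee, counted from awareness as now.
4. Check that 11.2 names the intended recipient and that the flow chart in 11.7 matches the revised text.

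The cost is an amendment to a few paragraphs. It adds no procedure, assessment or staff, and changes neither the data collected for the outcomes nor the analysis.

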#### 11.5 Significant Safety Issue (SSI)

A safety issue that could adversely affect participants' safety or materially impact the trial's continued ethical acceptability or conduct. The Human Research Ethics Committee and Sponsor's Delegate must be notified of all significant safety issues within 15 calendar days of the sponsor instigating or being made aware of the issue. SSI reports must be recorded in the [UNSW Safety Monitoring Register Template](#).

## **11.6 Urgent Safety Measure (USM)**

A measure that is taken to eliminate an immediate hazard to a participant's health or safety. Significant safety issues where an urgent safety measure is required to be taken to eliminate an immediate hazard must be classified as a significant safety issue requiring an urgent safety measure. The Human Research Ethics Committee and the Sponsor's Delegate must be notified of any significant safety issues that meet the definition of an urgent safety measure should be notified within 72 hours. Examples include:

- a serious adverse event that could be associated with the trial procedures and that requires modification of the conduct of the trial
- a patient population hazard, such as lack of efficacy of an intervention used for the treatment of a life-threatening disease.

USM reports must be recorded in the [UNSW Safety Monitoring Register Template](#).

## **11.7 Safety Assessment Flow Chart Investigational Medical Product Trials**

[figure not shown]

## 11.8 Register of Clinical Trial Safety Monitoring Reports

A register of all event reports assessed and classified is to be retained by the Coordinating Principal Investigator and reported to the trial sponsor annually and the HREC if required.

## 11.9 Reporting of Clinical Trial Safety Monitoring Reports

Single case reports of Adverse Events Adverse Reactions, Serious Adverse Events (SAEs), Serious Adverse Reactions (SARs), reports do not need to be reported to the UNSW Sponsor's Delegate or the HREC. All single case reports must be recorded in a safety monitoring register and are reported to the UNSW Sponsor's Delegate annually.

#### **a) Emerging Safety Issues**

The Trial Management Group (TMG) will oversee the day-to-day conduct of the trial. They will closely review all aspects of the conduct and progress of the clinical trial. They will meet on a regular basis to ensure that there is a forum for identifying and addressing issues; and more frequently on an informal basis if required. See minutes template (Attachment 13). The TMG will pay particular attention to progress towards clinical trial milestones (recruitment, timelines etc.); adherence to the protocol; and adherence to good research practices. The TMG is responsible for reviewing the safety information to identify any serious emerging safety concerns. If safety concerns are identified, this body, in consultation with [name] (Sponsor's Independent Physician/Medical Expert) will establish a plan to minimise the time participants may be placed at excess risk of harm. Before implementing the plan, the TMG must seek the advice of the human research ethics committee and sponsor's delegate.

#### **b) Annual assessment of safety**

The following information must be provided in a report to the sponsors delegate annually:

- Documented evidence that the Trial Management Group, Trial Safety Committee, or the Data Safety Monitoring Board (e.g. meeting minutes) confirmed that regular safety reviews occurred.
- Analysis of the trial intervention(s) and its implications for participants considering all available safety data and relevant clinical or non-clinical studies results.
- Any reports of emerging safety issues and a description of any measures taken or proposed to minimise risks.
- A copy of the safety monitoring register.

### **10. Non-compliance, Protocol Deviation and Serious Breaches of Good Clinical Practice**

#### **10.1 Protocol Deviation**

A protocol deviation is defined as any breach, divergence or departure from the requirements of Good Clinical Practice, the clinical trial protocol, the clinical trial standard operating procedures, or the human ethics approval that does not have a significant impact on the continued safety or rights of participants or the reliability and robustness of the data generated in the research or clinical trial. Protocol deviations are events that do not occur persistently or systematically and do not potentially result in participant harms. Examples of protocol deviations include but are not limited to:

- Deviations because of participant adherence to the protocol, including rescheduled study visits, participants refusal to complete scheduled research activities or failure to complete self-report questionnaires required by the study protocol.
- Blood samples obtained or clinical trial testing occurring at times close to, but not precisely at the time points specified in the protocol.
- The completion of consent forms, safety monitoring report, case report forms or data collection tools in a manner that is not consistent with the protocol instructions or failure to make reports within the required reporting timeframes.
- Administration of the clinical trial investigational medical product or device in a manner that is not consistent with the manufacturer's instructions for use.
- Use of an unapproved version of the participant information statement or recruitment of participants using unapproved recruitment procedures.
- Inclusion of a participant that does not meet the inclusion criteria.
- An urgent safety measure must be taken to eliminate an immediate hazard to a participant's health or safety.

## 10.2 Serious Breach of Good Clinical Practice

A serious breach is defined as a breach of Good Clinical Practice, the clinical trial protocol, the clinical trial standard operating procedures, or the human ethics approval that is likely to affect to a significant degree the safety or rights of participants or the reliability and robustness of the data generated in the clinical trial. Examples of serious breaches include but are not limited to:

- Persistent or systematic non-compliance with the instructions for completing consent forms, safety monitoring forms, case report forms or data collection tools that result in continued missed or incomplete data collection.
- Failure to record or report adverse events, serious adverse events, suspected unexpected serious adverse reactions, significant safety issues where urgent safety measures were implemented.
- Failure to conduct clinical trial procedures following the clinical trial delegation log.
- Widespread and uncontrolled use of protocol waivers affecting eligibility criteria, which leads to harm to trial subjects.
- Failure to report investigational medical product or device defects to the clinical trial sponsor or any relevant regulatory body.
- Failure to conduct research following the issued approvals, permits or licences by required laws, regulations, disciplinary standards, and UNSW policies relating to the responsible or safe conduct of research.
- Concealing or facilitating breaches (or potential breaches) of the Research Code by others.
- Researching without the requisite approvals, permits or licences required by laws, regulations, disciplinary standards, and UNSW policies related to the responsible or safe conduct of research.
- Failure to conduct research as approved by an ethics review body where that conduct leads to (or has the potential to) results in participant harms.
- Researching without ethics approval as required by the National Statement on Ethical Conduct in Human Research where that conduct leads to (or has the potential to) result in participant harms.
- Any breaches as outlined in the UNSW Research Misconduct Procedure or the Australian Code for responsible conduct of research that leads to (or can potentially) result in participant harms.

## 10.3 Reporting Protocol Deviations

- Protocol deviations occurring at a site must be documented in site files and reported by the principal site investigator to the Coordinating Principal Investigator.
- The Coordinating Principal Investigator must review the protocol deviation and the clinical trial protocol to establish the corrective actions and preventative steps to prevent the deviation from reoccurring.
- The protocol deviation and corrective action plan must be reported to the UNSW Sponsor's Delegate by the Coordinating Principal Investigator or Coordinating Research Team using the protocol deviation report form.

